#### Secondary outcomes

Table 1 lists all secondary outcomes for addressing objectives 2–5, including their specific measurement variables, analysis metric/approach and, where appropriate, the method of aggregation; no continuous outcomes will be analysed as categorical. Time points for each outcome can be found in Fig. 2.

##### Sample size

The accepted minimal clinically important difference for effect of a direct novel disease modifying therapy for RA is a change of 1.2 points on the DAS28 [57]. As our intervention is modifying disease indirectly, we are anticipating a smaller target difference of 0.6 points in the DAS28, with an expected standard deviation of 1.2 [57].

In the absence of established methodology for sample size calculations for trials with a continuous recruitment short exposure design, we used the ShinyCRT calculator [58, 59] with the cross-sectional design setting to produce a conservative (i.e. greater) sample size estimate. We estimated that we needed to include 432 patient participants in the analysis (i.e. 27 participants per cluster) to achieve at least 90% power for detecting the target difference under the following assumptions: a discrete time decay within-cluster correlation structure; varying cluster sizes with a coefficient of variation of cluster size of 0.15 (based on accruing roughly 27 ± 4 patient participants per cluster); a between-groups a type-I error rate (alpha) of 0.05; an intra-class correlation (ICC) of 0.05; a cluster auto-correlation of 0.8; and 16 clusters switching over in pairs of two across eight steps. In the absence of available shared datasets and published trials relevant to ours, we formulated our assumptions regarding the ICC and cluster auto-correlation in consultation with the clinical trial design expert on the REMORA2 programme steering committee (see under ‘ Oversight and monitoring’ below), who advised on commonly used and relatively conservative figures that would give us ample sample size in a range of potential scenarios.

Based on findings from the feasibility trial [32], we anticipate 30% of recruited patient participants allocated to the intervention group may not initiate symptom tracking, with a further 15% across both groups being lost to follow-up due to drop-out/withdrawal. To compensate for this attrition and achieve the required analysis sample size of 432, we aim to recruit a total of 736 participants (i.e. 46 per site).

There are no formal interim analyses planned, thus we do not anticipate any adjustments to the sample size.

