### Statistical methods

#### Statistical methods for primary and secondary outcomes

This section summarizes the planned statistical methods for the primary and secondary quantitative outcomes listed in Table 1. For all analyses described below, we will take an intention-to-treat approach, i.e. we will include participants in the treatment group they are assigned to regardless of the extent to which they take up or adhere to the intervention. Further details, including on methods for qualitative outcomes, will be provided in the full statistical analysis plan, which we will draft with input from the trial’s programme steering committee and publish before we lock the trial data set.

We will report the trial results in accordance with the CONSORT stepped wedge trial extension [60].

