#### Methods for interim and additional analyses

Since we are expecting engagement with integrated symptom tracking to vary between patient participants in the integrated symptom tracking group, we will conduct and report sensitivity analyses for ‘best-case’ and ‘worst-case’ scenarios, i.e. assuming very high and very low engagement across participants, respectively.

There are no formal interim or subgroup analyses planned.

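### The sample size treats the 30% who never start tracking as lost from the analysis, but the intention-to-treat rule keeps them in, so the stated power does not describe the planned analysis

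*Protocol article*

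**What the plan says.** The Sample size section plans for a between-group difference as follows: "we are anticipating a smaller target difference of 0.6 points in the DAS28, with an expected standard deviation of 1.2". The reason given for going below the accepted 1.2 points is that the intervention modifies disease indirectly; uptake is not mentioned. From this, with a stepped-wedge calculator, the protocol concludes that "we needed to include 432 patient participants in the analysis (i.e. 27 participants per cluster) to achieve at least 90% power".

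The same section then turns to expected losses. From the feasibility trial, "we anticipate 30% of recruited patient participants allocated to the intervention group may not initiate symptom tracking", and a further 15% across both groups are expected to be lost to follow-up. The two are combined: "To compensate for this attrition and achieve the required analysis sample size of 432, we aim to recruit a total of 736 participants", which is 46 per site.

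The analysis set is fixed under Statistical methods for primary and secondary outcomes, where the ITT approach for all analyses is spelled out: "we will include participants in the treatment group they are assigned to regardless of the extent to which they take up or adhere". Consistent with this, Criteria for discontinuing or modifying allocated interventions says that patients who do not use the intervention as intended are not automatically withdrawn and are still asked for data.

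**The concern.** Not starting the app and being lost to follow-up have different consequences under ITT. A patient lost to follow-up contributes no observed outcome. A patient who never opens the app still attends clinic, still has a DAS28-CRP recorded, and is analysed in the intervention group. That patient does not reduce the analysed number but may reduce the average difference between groups.

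The sample size handles the second kind of patient as if they were the first. So the analysed number of 432 is not the number the ITT analysis would contain, and the power attached to 432 belongs to a different analysis. The inflation also departs from its own premise: the 30% is stated for one group but has been applied to everyone.

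At stake is how the result will be read. If the true ITT difference is a diluted one, a null result would be judged against a power claim that the analysis may not meet. If 0.6 was always meant as the ITT difference, recruitment was inflated for a loss that does not occur.

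**Working it through.** **Inputs, all from the Sample size section unless noted.** Difference 0.6; SD 1.2; ICC 0.05; cluster auto-correlation 0.8; "a discrete time decay within-cluster correlation structure"; coefficient of variation of cluster size 0.15; alpha 0.05 (taken as two-sided, in line with the 95% intervals under Primary outcome analysis); 16 clusters in eight pairs. The legend to Fig. 1 gives 27 weeks of recruitment, which is nine 3-week periods, so 16 x 9 = 144 cluster-periods, half of them (72) under intervention. 432/144 = 3 analysed patients per cluster-period.

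**Method.** Generalized least squares variance of the treatment effect on cluster-period means, with fixed period effects. Between-cluster variance is 0.05 x 1.2² with correlation 0.8^|t−s| between periods t and s; residual variance is 0.95 x 1.2²/m for m patients per cluster-period. Power = Φ(difference/SE − 1.96).

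**1. The protocol's own power.** N = 432, difference 0.6: SE = 0.173, 0.6/0.173 = 3.47, power 93% (also 93% with the cluster-size variation of 0.15). This supports the stated figure of at least 90%, so the model is a fair stand-in for the sponsor's calculation.

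**2. The protocol's own recruitment target.** 27/(0.70 x 0.85) = 45.4, rounded up to 46 per site; 46 x 16 = 736. This matches exactly, and it applies the 30% to all recruits. With half of cluster-periods under intervention, 30% in that group alone is 15% overall, so excluding non-initiators as described would need 432/(0.85 x 0.85) = 598.

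**3. The number in the ITT analysis.** Only the 15% are lost: 736 x 0.85 = 626. At this N, SE = 0.1505.

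**4. Power with 626 analysed, before baseline adjustment.**

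| What 0.6 means | ITT difference | Power |
|---|---|---|
| Effect in initiators; non-initiators gain nothing | 0.7 x 0.6 = 0.42 | 80% |
| ITT difference already | 0.60 | 98% |

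Dilutions of 15%, 20% and 25% instead of 30% give 92%, 89% and 85%. The ITT difference detectable with 90% power is (1.96 + 1.28) x 0.1505 = 0.49, which is 0.49/0.7 = 0.70 among initiators if non-initiators gain nothing.

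**5. Why dividing by 0.7 does not repair dilution.** Required N varies with 1/difference². A difference shrunk to 0.7 of its size costs 1/0.7² = 1/0.49 = 2.04 in N, not 1/0.7 = 1.43. In this design it costs somewhat more, because between-cluster variance does not fall as more patients are added per cluster: 90% power needs about 364 analysed at 0.6 and about 953 at 0.42.

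**6. If 0.6 is the ITT difference.** Non-initiation needs no allowance: 432/0.85 = 508.2, so about 509 recruits would keep the 432 the protocol requires.

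**7. Sensitivity.** With a t reference on 14 degrees of freedom, the stated case is 90% (89.7%), the diluted case 74% and the undiluted case with 626 analysed 96%. Block-exchangeable or exchangeable correlation gives 82% for the diluted case. The primary model adjusts for baseline DAS28-CRP, but no baseline correlation r is given. Taking SD x √(1 − r²) with assumed r of 0.3, 0.5 and 0.6, the diluted case becomes 83%, 90% and 94%.

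**The case against.** The strongest reply is that 0.6 is simply the between-group target difference. The Sample size section does not restrict it to initiators, the primary outcome is a between-group difference in marginal means, and the analysis is ITT. On that reading 626 analysed gives 98% and the trial is not short of power. This stands as a possible reading, and it is why a reader should not infer that true power is 80%. That figure needs two assumptions the protocol does not state: that 0.6 applies to initiators only, and that non-initiators gain exactly nothing. The first is suggested by removing non-initiators to arrive at the 432 powered for 0.6, but it is not written down.

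Nor should a reader infer that 736 cannot be squared with at least 90% power on any reading. It can: 98% if 0.6 is the ITT difference, and about 96% if non-initiators really were excluded (736 x 0.85 x 0.85 = 532 analysed). On those readings the fault is surplus recruitment or a conflict with the ITT rule, not lost power.

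It is also fair that the calculation takes no credit for baseline adjustment, that applying the 30% to both groups errs towards more patients, and that confidence intervals will show the precision achieved whatever was planned. The worry that an analysed number of 432 might push analysts to drop non-initiators is weak, since the protocol fixes ITT and keeps collecting their data.

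None of this removes the mismatch. If 0.6 is the ITT difference, the 30% inflation has no basis. If it is not, the power is lower than stated unless baseline adjustment makes up the gap. The point cannot be left to the analysis plan, because the target difference, the inflation and the analysis set are all fixed in this document.

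**Conclusion.** The concern holds. The sample size describes an analysis without the non-initiators; the protocol specifies one with them. About 626 would be analysed rather than 432, and the intervention-only 30% was applied to both groups to reach 736.

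The stated power therefore does not describe the planned analysis. On the protocol's own ICC, auto-correlation and SD, and before baseline adjustment, power with 626 analysed lies between about 80% (ITT difference 0.42) and about 98% (ITT difference 0.6), depending on what 0.6 means and on how much non-initiators benefit. The 80% is not a lower bound on what the adjusted model will deliver: an assumed baseline correlation of 0.5 brings the diluted case back to about 90%, but the protocol states no correlation.

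The ITT analysis itself is sound. What is wrong is the sample-size justification.

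**What to change.** In the Sample size section:

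- Stop describing non-initiation as attrition. State that non-initiators remain in the ITT set and that, with 15% loss, about 626 of 736 recruits are expected to be analysed.
- Say whether 0.6 is the ITT difference or the effect among those who start tracking.
- Restate power on that basis: about 98% for an ITT difference of 0.6, about 80% for 0.42, or an ITT difference of 0.49 detectable with 90%. These are before baseline adjustment; if credit is taken for it, state the correlation assumed.
- If 0.6 is the ITT difference, acknowledge that the 30% inflation was not needed.

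The cost is a text change and one recalculation, with no extra patients and no change to the primary analysis. The downside is that the stated power may become less favourable.

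The engagement scenarios under Methods for interim and additional analyses ("assuming very high and very low engagement across participants, respectively") can stay. They are sensitivity analyses and do not bear on the power basis. A complier-average analysis could be added as a supplement, since controls have no access to the app, but that is optional and not part of this correction.

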### Data collection and management

#### Plans for assessment and collection of outcome and other data

Table 1 lists the data collection methods and study instruments for all outcomes, with Fig. 2 showing when assessments take place. The sections below further describe the data collection methods.

##### Electronic questionnaire for healthcare professional demographics

After completing the training and providing informed consent, healthcare professionals participating in the trial receive an invitation via email to complete an online questionnaire on their demographics (age, gender, ethnicity, role, years of rheumatology experience).

##### Electronic health record data extraction

Delegated staff at clusters use an eCRF to enter data extracted from the electronic health record system on clinician-reported disease activity, joint involvement and severity and medication and resource use. For the baseline assessment, this additionally includes patient demographics (gender, date of birth, ethnicity, smoking status, body mass index) and comorbidities.

The baseline assessment is based on information recorded for the clinic visit on, or closest to, the date of recruitment, but within a time window of 6 months prior to or 1 month after consent. Follow-up assessments are performed at each clinic visit during the 12 ± 3-month follow-up window but since these visits are scheduled by the care team as required, no pre-defined schedule of follow-up data extractions has been set.

Healthcare professionals complete paper versions of the eCRFs during follow-up visits to aid data collection.

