As it is not possible to blind patients from the intervention, they receive information about their allocation upon consenting to take part; allocation is managed by the study team. Patient-facing materials have been designed to present the control and intervention conditions in equipoise as much as possible to minimize influence on treatment beliefs. Similarly, it is not possible to blind healthcare professionals directly responsible for patient care due to patient-reported symptom data becoming available in the interactive dashboard once patient participants start tracking as part of the intervention.

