**Fig. 3 Fig3:**
[figure not shown]
SPIRIT diagram of schedule of activities. Abbreviations: Brief IPQ: Brief Illness Perception Questionnaire; CDAI: Clinical Disease Activity Index; CollaboRATE: share decision making questionnaire; COM-B: Capabilities, Opportunities, Motivations for Behaviour change questionnaire; DAS28: Disease Activity Score for 28 joints; EQ-5D-5L: EuroQol five-dimension scale questionnaire; HAQ: Health Assessment Questionnaire; PEI: Patient Enablement Instrument; RAID: Rheumatoid Arthritis Impact of Disease score; RAPID-3: Routine Assessment of Patient Index Data 3; WPAI-RA: Work Productivity and Activity Impairment Questionnaire: Rheumatoid Arthritis. **a** Frequency and time points of follow-up appointments are scheduled by the rheumatology team and according to clinical need. No additional visits are mandated as part of the REMORA2 trial. Procedures listed reflect the maximum number of expected activities; **b** Clinical data extracted from the electronic health record at t_0_ comprises data collected at the most recent appointment within the period from 6 months before or 1 month after the time of allocation; **c** For patients who have a clinic visit between months 9 and 12, the REMORA app is deactivated after 12 months. Those who do not have a clinic visit in this period are asked to continue tracking their symptoms beyond 12 months, with the REMORA app being deactivated as soon as they had their final clinic visit; **d** Assessments take place throughout the follow-up phase with participants only being interviewed/observed once; **e** Intervention group only

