##### Patient web survey

We use an electronic questionnaire to collect patient-reported data from patient participants on disease activity, joint involvement and severity, work impairment, quality of life, disability, experience of care, self-management, understanding of their RA, resource use and travel time and costs related to in-person rheumatology outpatients visits. The baseline assessment additionally includes patient demographics (year of birth, gender, ethnicity, smoking status, postcode (to derive level of relative socio-economic deprivation), income, educational attainment).

For the baseline assessment, all patient trial participants receive instructions for completing the questionnaire at the time of allocation (irrespective of allocation group). Follow-up assessments take place at 3, 6, 9 and 12 months post-allocation.

There is an additional online questionnaire at 6 months asking patient participants to share their thoughts on the benefits of a range of potential future developments/uses of integrated symptom tracking.

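### Two conflicting rules define the baseline DAS28-CRP visit, and both allow a post-allocation score to serve as the baseline covariate

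*Protocol article*

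**What the plan says.** The Protocol article defines the health-record baseline twice.

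- Under Electronic health record data extraction, the visit nearest recruitment supplies the baseline, and its date must lie "within a time window of 6 months prior to or 1 month after consent".
- In footnote b of Fig. 3 (Participant timeline), the t0 extraction "comprises data collected at the most recent appointment within the period from 6 months before or 1 month after the time of allocation".

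Under Concealment, implementation and blinding, patients are unblinded: "they receive information about their allocation upon consenting to take part". The same section says of clinicians that "it is not possible to blind healthcare professionals directly responsible for patient care". Under Patient web survey, "all patient trial participants receive instructions for completing the questionnaire at the time of allocation", in both groups.

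Under Primary outcome analysis, baseline DAS28-CRP is a named predictor. Under Secondary outcome analyses, continuous outcomes are handled in a similar way, while the models for categorical outcomes leave baseline values out. Table 1 derives the EULAR response categories from DAS28-CRP.

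**The concern.** A covariate is a true baseline only if neither the treatment nor knowledge of it can have moved it. Here a visit up to a month after allocation can supply the value. By then an intervention patient may be tracking symptoms and a clinician may have the dashboard open. DAS28 includes joint counts and a global assessment, which unblinded people report or score. Adjusting for such a value can remove part of the treatment effect or distort it. It also makes EULAR response a change from a value that may already be affected, even though the categorical models carry no baseline term.

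Separately, one patient can have two different baseline values depending on which passage the data extractor follows. That needs no assumption about bias: a named covariate of the primary model is not uniquely defined.

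For patient-reported outcomes, group disclosure and the baseline survey invitation are both placed at about the same moment, and nothing requires the survey to be finished first.

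**Working it through.** **1. The plan's own figure, for scale.** Inputs from Sample size: 16 clusters, 8 steps (9 periods), 27 analysed per cluster (3 per cluster-period), SD 1.2, ICC 0.05, cluster auto-correlation 0.8 with discrete time decay, difference 0.6, alpha 0.05 (taken as two-sided). With equal cluster sizes and fixed period effects, generalised least squares gives a standard error of 0.173. Power = Φ(0.6/0.173 − 1.96) = 93.4%, which agrees with the stated minimum of 90%.

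**2. The two selection rules side by side** (illustrative visit patterns, timed from consent/allocation):

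| Visits | Text: nearest visit | Fig. 3: latest visit |
|---|---|---|
| Day of consent; 3 weeks after | Day of consent | 3 weeks after |
| 1 week before; 3 weeks after | 1 week before | 3 weeks after |
| 10 weeks before; 3 weeks after | 3 weeks after | 3 weeks after |

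The rules disagree only when the earlier visit is nearer and the later one falls within a month, so the two visits must lie less than 2 months apart. The third row shows that the nearest-visit rule does not exclude post-allocation values either.

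**3. How many patients.** The Introduction gives visits every 3–12 months. If recruitment falls at a random point between regular visits L months apart, the chance of a visit in the following month is 1/L: 1/12 = 8% to 1/3 = 33%. Recruitment in clinic lowers this; more frequent visits for active disease raise it. The protocol gives no actual share.

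**4. Bias for DAS28-CRP.** The adjusted difference is approximately (difference in follow-up means) − b × (difference in baseline means). If a share f of intervention baselines already carries an improvement s, the estimate loses b × f × s. All three inputs are assumptions.

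- b = 0.5, f = 10%, s = 0.1: 0.5 × 0.10 × 0.1 = 0.005 points.
- b = 0.5, f = 1/3, s = 0.3: 0.05 points.
- b = 0.5, f = 40%, s = 0.3: 0.06 points, which is 0.06/0.6 = 10% of the target and 0.06/0.173 = 0.35 of a standard error. Power = Φ(0.54/0.173 − 1.96) ≈ 88%.
- Extreme corner, b = 0.7, f = 50%, s = 0.3: 0.105 points, power 81.6%. This f exceeds the 33% in step 3.
- f = 0 or s = 0: no loss.

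If knowledge of the group shifted early scores the other way, the sign would reverse.

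**5. Survey outcomes.** Suppose knowing the group shifts reported scores by d0 at baseline and d1 at follow-up. The adjusted estimate is then the true effect + d1 − b × d0. With an assumed b = 0.6 and d0 = 0.1 SD, the error is −0.06 SD if the shift has gone by follow-up (d1 = 0), but 0.1 − 0.06 = +0.04 SD if it persists (d1 = 0.1). In the second case the unadjusted error would be +0.1 SD, so adjustment reduces it.

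**The case against.** The best defence of the plan has four parts.

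- **Mechanism.** Tracked data are reviewed only at visits, and better treatment decisions are the main proposed route to benefit. A DAS28-CRP taken at the first dashboard visit cannot reflect decisions made at that visit. Only a second visit within the month, early self-management or unblinded scoring could move it. Set-up also takes time (up to five reminders), and 30% of the intervention group may never start tracking. An early shift of 0.3, half the 12-month target, has no support in the protocol. This stands, and is why the bias is probably small.
- **Frequency.** On the protocol's own visit interval, two visits less than 2 months apart are unusual, so the two rules will seldom conflict. This largely stands, although the trial enrols active disease and gives no visit frequency for it.
- **Rationale.** The trial mandates no extra visits, so a flexible window limits missing and stale baselines. This is a fair trade-off, but it does not explain two different rules.
- **Surveys.** Patient materials present both conditions in equipoise, and adjustment can partly cancel reporting bias (step 5). This stands too.

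A reader might infer that all survey baselines are completed after patients know their group. The protocol does not say so. It places disclosure upon consent and the survey instructions at allocation, without giving the order. What can be said is that nothing secures completion beforehand.

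**Conclusion.** The point holds on the wording. The two passages give different selection rules, and both admit a post-allocation DAS28-CRP as the baseline covariate of the primary model and as the starting value for EULAR response. Their anchors also differ (consent and allocation), though these nearly coincide because patients learn their group on consenting.

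The size of any bias cannot be computed, because the protocol gives neither the share of late baselines nor any early shift. About 0.06 points or less is a reasonable bound under generous assumptions, a slope of 0.5 among them; a slope of 0.7 with a one-third share and a shift of 0.3 would give 0.07. It is nil without an early shift, and the direction is uncertain.

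A reader might conclude that the primary result will be materially diluted, or that survey outcomes carry a known bias of fixed sign. The documents support neither: every magnitude rests on assumed inputs, and the survey error can take either sign. This is worth correcting because the remedy is cheap, not because it threatens the trial.

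**What to change.** **DAS28-CRP.** Before data lock, reconcile the data extraction text and Fig. 3 footnote b to one rule: the last DAS28-CRP on or before the consent/allocation date and within the preceding 6 months. Treat later values as missing baseline under the multiple imputation already planned, use the same value as the EULAR reference, and report the present window as a sensitivity analysis.

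The cost is somewhat more missing or older baseline values. With regular visits every L months, a baseline is newly lost only if the next visit falls within 1 month and the previous one was more than 6 months ago, a share of min(1, L − 6)/L for L above 6. That is none up to L = 6, at most 1/7 = 14% at L = 7, and 1/12 = 8% at L = 12; recruitment at clinic visits lowers it.

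**Survey outcomes.** Record each baseline survey date relative to disclosure of allocation. Add a sensitivity analysis that does not adjust for baselines completed after disclosure and keeps all patients. The cost is some precision in that analysis.

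Two alternatives are worse. Changing the order of e-mails midway would tie the baseline procedure to the arm. Recruitment began on 10 July 2024 and the article appeared on 15 October, about week 14, in period 5. With sequence s switching after period s, control cluster-periods by sequence number 8+7+6+5+4 = 30 of 40 (75%) in periods 1–5 and 3+2+1+0 = 6 of 32 (19%) in periods 6–9. Excluding patients whose survey followed disclosure could remove much of the sample.
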